## 4. Study Design

### **4.1 Patient Population**

This study will be a single-center observational study involving patients admitted to the intensive care unit at Health Sciences Centre with acute traumatic spinal cord injury (ASIA A, B or C). All patients will undergo placement of an intraspinal pressure monitor within 24hrs of arrival. Physiological recordings will occur during the SICU stay for a maximum duration of 5 days (or until discharge from the intensive care unit).

Given that this is a feasibility and validation study, we will recruit patients over 2 years and anticipate that 20 patients will be enrolled during this time frame. Upon admission, patients will be screened for inclusion in the study based on the inclusion and exclusion criteria listed in *Section 5*. Initial demographic information, medical history, physical examination and imaging findings will be recorded using standardized data collection forms for all patients that consent to participation in the study. Patients will then be taken for surgical intervention within 24hrs of admission, and an intraspinal pressure monitor will be inserted as part of the overall surgical procedure. Initial intraspinal pressure readings will be recorded intraoperatively. Standardized data collection forms will then be used to collect pertinent data related to the surgical intervention and any intraoperative adverse events. Similarly, postoperative adverse events will be collected for the first 30 days following surgical intervention.

### **4.2 Physiologic Data Capture and Processing**

Once surgical intervention has been completed, the patient will be monitored in the intensive care unit as long as deemed necessary by care providers. During this time in SICU, intraspinal pressure and physiological parameters such as heart rate, respiratory rate, blood pressure, and mean arterial pressure will be captured at the bedside using a secure laptop with ICM+ software.

Both ABP and ISP will be obtained through invasive methods, with all signals recorded in high-frequency time series, sampled at 100 Hz or higher through and analogue to digital signal converters (DT9804 or 9T9826; Data Translations, Marlboro, MA), using ICM+ software (Cambridge Enterprise Ltd, Cambridge, UK, http://www.neurosurg.cam.ac.uk/icmplus) connected to our SICU monitors. Signals from all of the monitoring devices described below are subsequently recorded in time series using this software over the course of the recording periods described above. All physiologic signals from monitoring devices within the SICU for neurologically ill patients are currently recorded and archived as part of a separate prospective signal database study that will be ongoing at HSC (HS20840; H2017:181). Arterial blood pressure (ABP) will be obtained through either radial or femoral arterial lines connected to pressure transducers (Baxter Healthcare Corp. CardioVascular Group, Irvine, CA). ICP will be acquired via an intra-parenchymal strain gauge probe (Codman ICP MicroSensor; Codman & Shurtleff Inc., Raynham, MA).

Post-acquisition processing of the above signals will be conducted using ICM+ software. SCPP will be calculated using the formula: SCPP = MAP – ISP. Systolic ABP (ABPs) will be determined by calculating the maximum ABP over a 1.5 second window, updated every second. Similarly, diastolic ABP (ABPd) will be determined by calculating the minimum ABP over a 1.5 second window, updated every second. Pulse amplitude of ISP (sAMP) will be determined by calculating the fundamental Fourier amplitude of the ICP pulse waveforms over a 10 second window, updated every 10 seconds.

Ten-second moving averages (updated every 10 seconds to avoid data overlap) will be calculated for all recorded signals: ISP, ABP (which produced MAP), ABPs and ABPd. Ten-second moving averages will be calculated in order to focus on slow waves of parent signals, decimating the frequency to the range associated with vascular autoregulation.

Spinal vascular reactivity indices will be derived as follows: a moving Pearson correlation coefficient will be calculated between ISP and MAP using 30 consecutive 10-second windows (i.e. five minutes of data), updated every minute. This index will be referred to as the spinal pressure reactivity index (sPRx). Similarly, other vascular reactivity metrics will be derived using the correlations between slow-waves of sAMP and MAP (creating spinal pulse amplitude index; sPAx) and sAMP and SCPP (creating sRAC; R = correlation, A = pulse amplitude of ISP, C = SCPP). Finally, the spinal compensatory reserve will be assessed by deriving the spinal RAP index (sRAP), using the moving Pearson correlation between sAMP and ISP. Data for further analysis will be provided in the form of a minute by minute time trends, output into comma-separated values (CSV) datasets.

### ***4.3* Motor Evoked Potentials**

In patients undergoing evaluation for motor evoked potential monitoring, we will capture transcranial magnetic motor evoked potentials within the 24 hours pre-operatively, 24hrs post-operatively and again during the standardized functional assessments at 1, 3, 6, 9 and 12 months.

***4.4 Functional Outcome Assessments***

Each patient will then undergo standardized functional assessments at 1, 3, 6, 9, and 12 months following the acute injury. Functional assessments will include assessment of the ASIA impairment scale, functional independence score (FIM) and Quality of Life Index for Spinal Cord Injury (QLI-SCI). We may also use information captured in the Rick Hansen Spinal Cord Injury Registry, which is a national database that collects functional outcomes and adverse events on patients with traumatic spinal cord injury. This registry is currently approved by the University of Manitoba Research Ethics Board (Ethics # H2005:173(HS14502)).

**5.** Study Enrollment and Withdrawal

In this study, we aim to enroll 20 patients over the course of 2 years to evaluate the role of intraspinal pressure monitoring in the management of acute spinal cord injury. As described above, patients with acute traumatic spinal cord injury will be identified at the time of admission to the Health Sciences Center.

***5.1 Inclusion Criteria***

In order to participate in this study, patients must meet all of the following criteria:

- patients with acute traumatic spinal cord injury ASIA A, B or C
- spinal vertebral level between C0-L1
- age between 18–70yrs

### **5.2 Exclusion Criteria**

Any patients meeting the exclusion criteria below will be excluded from study participation.

- patients with cauda equina syndrome or radicular injury only
- patients presenting to HSC >48hrs from time of spinal cord injury
- patients unable to communicate in the English language
- pre-existing cognitive impairment
- penetrating spinal cord injury
- a pre-existing neurodegenerative disorder involving brain or spinal cord
- patients with concomitant injuries requiring emergent surgical intervention
- patients with injuries to the chest, abdomen, pelvis or extremities, which would impair a clinician’s ability to discern the severity of the injury
- history of coagulopathy
- pre-existing infection
- pregnancy

### **5.3 Strategies for Recruitment and Retention**

Research nurses/assistants will be employed to continually scan patient lists in the intensive care unit to identify potential candidates. Long-term retention of patients in the study will be supported via dedicated clinic follow-ups with patients. During these clinic visits, we will encourage and assist patients with the completion of standardized questionnaires. Patients will not be compensated for participation in this study.

### **5.4 Subject Withdrawal**

Study patients may withdraw voluntarily from the study, or the investigator may terminate the patient’s participation in the study if:

- a medical condition or event occurs such that ongoing participation in the study would not be in the best interest of the patient
- the subject meets an exclusion criterion (either newly developed or previously not recognized) that precludes further study participation

In situations where a patient is withdrawn from the study, complete adverse events data will be captured and stored in case of future need. We will then aim to extend the duration of the study until the study participant can be replaced with another patient meeting the inclusion criteria for the study.

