2. Prospectively evaluate the overall relationship between spinal cord perfusion pressure and functional outcomes in patients with acute traumatic spinal cord injury.
   1. HYPOTHESIS: There will be a general positive relationship between both SCPP and individual optimal SCPP, with patient functional outcome in acute traumatic spinal cord injury.
3. Evaluate the relationship between SCPP, motor evoked potentials and functional outcomes after *incomplete* spinal cord injury.
   1. HYPOTHESIS: Time spent with SCPP near individual optimal SCPP will be directly associated with improved motor evoked potentials and functional outcomes in *incomplete* spinal cord injury.

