**Intraspinal Pressure Monitoring Visits (POD#1 to POD#5)**

Following surgery, each patient will be visited daily to conduct the following study related procedures:

- ensure no change to clinical status of the patient that would warrant termination of that patient’s involvement in the study
- verify that the intrapsinal pressure monitor is in situ and recordings are being captured continuously
- verify continuous monitoring of physiological data
- conduct transcranial magnetic motor evoked potential testing and record findings on neurophysiological monitoring report form
- document any medical or surgical adverse events
- document any protocol violations -document laboratory investigations including blood chemistry, hematology and medication use.

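### After the investigator ends a patient's participation, Section 5.4 provides for adverse-event capture and replacement but not for the 1- to 12-month ASIA, FIM and QLI-SCI assessments

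*Protocol*

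**What the plan says.** Protocol Section 5.4 describes exit from the study in one form: "Study patients may withdraw voluntarily from the study, or the investigator may terminate the patient’s participation in the study if" one of two conditions is met. The first is that "a medical condition or event occurs such that ongoing participation in the study would not be in the best interest of the patient". The second is that "the subject meets an exclusion criterion (either newly developed or previously not recognized) that precludes further study participation".

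The section then states what follows: "In situations where a patient is withdrawn from the study, complete adverse events data will be captured and stored in case of future need". After that comes replacement: "We will then aim to extend the duration of the study until the study participant can be replaced with another patient" who meets the inclusion criteria. ASIA, FIM and QLI-SCI are not mentioned.

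Section 6.2, under the monitoring visits on POD#1 to POD#5, asks staff each day to "ensure no change to clinical status of the patient that would warrant termination of that patient’s involvement in the study". The object of that check is study involvement, not the recording alone.

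Functional outcome is scheduled at 1, 3, 6, 9 and 12 months (Section 4.4). It serves secondary objective 2, "Prospectively evaluate the overall relationship between spinal cord perfusion pressure and functional outcomes in patients with acute traumatic spinal cord injury", and secondary objective 3, which concerns incomplete injury. Section 8.3 relates the physiological measures to these outcomes by linear and logistic regression.

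**The concern.** The study has two separable parts: invasive recording for at most 5 days, and functional assessment for a year. A medical reason to end the first is often no reason to end the second, yet Section 5.4 does not say that a patient whose participation the investigator has ended is still to be assessed.

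The first trigger is a medical condition or event, which may well go with a poor clinical course. Missing outcomes could then depend on the outcome itself, and the relation between SCPP and recovery would be estimated in a selected group. Replacement brings the count back to the planned 20 without bringing back the missing outcomes, so a full-looking sample could conceal the selection.

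This belongs in the protocol. An analysis plan can choose how to handle missing data, but it cannot recover assessments that nobody made.

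**Working it through.** **1. What ends recording, and what ends follow-up**

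| Event | Where | Functional follow-up afterwards |
| --- | --- | --- |
| Discharge from intensive care, or 5 days of recording | Section 4.1 | Continues (4.4 and 6.2) |
| Probe removal on POD#6 | Section 6.2 | Continues (6.2, follow-up visits) |
| Investigator ends participation | Section 5.4; daily check in 6.2 | Not provided for; adverse events only, then replacement |

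The gap is confined to the last row. The one other source of functional outcomes is the national registry in Section 4.4. Its use is optional and is not linked to withdrawn patients.

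**2. The exclusion-criterion trigger**

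Section 5.4 speaks of criteria that develop newly. Several criteria in Section 5.2 are facts at entry: infection and cognitive impairment are qualified as pre-existing, and coagulopathy as a history. As worded, these cannot arise later. The two sections need to be reconciled. The more likely route to outcome-related exit is the medical-event trigger.

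**3. Possible size (illustration)**

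The protocol has no figure to reproduce. The 20 patients are an accrual expectation, and no withdrawal rate, outcome distribution or effect size is given. Everything below rests on assumed values.

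*Correlation and slope.* Let SCPP and outcome Y be standard bivariate normal with true correlation ρ = 0.50. Suppose a fraction k of the patients in the worst share q of outcomes is lost. With a the q-quantile of the normal distribution and f its density at a:

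- retained share R = 1 − kq
- mean of Y in retained patients m = kf/R
- E(Y²) = [(1 − q) + af + (1 − k)(q − af)]/R, and V = E(Y²) − m²
- slope ratio s = V/(ρ²V + 1 − ρ²)
- observed correlation = ρ√s

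| q | k | a | f | m (SD) | V | s | Correlation |
| --- | --- | --- | --- | --- | --- | --- | --- |
| 0.20 | 0.5 | −0.842 | 0.280 | 0.16 | 0.845 | 0.845/(0.211 + 0.75) = 0.88 | 0.47 |
| 0.10 | 1 | −1.282 | 0.175 | 0.19 | 0.712 | 0.712/(0.178 + 0.75) = 0.77 | 0.44 |
| 0.20 | 1 | −0.842 | 0.280 | 0.35 | 0.583 | 0.583/(0.146 + 0.75) = 0.65 | 0.40 |

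If withdrawal is unrelated to outcome, m = 0, s = 1 and the correlation stays at 0.50.

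*Share improved.* Let p be the true share improved, and w_b and w_g the withdrawal probabilities in patients who do badly and well. The share seen in completers is p(1 − w_g)/[p(1 − w_g) + (1 − p)(1 − w_b)]. With w_g = 0:

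| True share | w_b = 10% | w_b = 20% | w_b = 30% |
| --- | --- | --- | --- |
| 20% | 21.7% | 23.8% | 26.3% |
| 30% | 32.3% | 34.9% | 38.0% |
| 40% | 42.6% | 45.5% | 48.8% |

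The overstatement is about 2 to 9 points. With w_g = w_b it is zero.

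*What replacement hides.* Suppose 6 of 20 completers improve (30%). With 2 patients withdrawn and replaced, the share among all 22 enrolled lies between 6/22 = 27.3% and 8/22 = 36.4%. With 4 it lies between 6/24 = 25.0% and 10/24 = 41.7%. The 20 completers alone show none of this uncertainty.

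**The case against.** Much of the case on the other side stands.

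- A reader might infer that stopping monitoring always means leaving the study. The documents do not support that: recording ends at intensive care discharge or after 5 days, and follow-up goes on.
- A reader might infer that outcomes are certain to be lost. Section 5.4 does not forbid further assessment; it only fails to provide for it. Termination is at the investigator's discretion, and the exclusion criterion must be one that rules out continuing. A late infection or pregnancy does not plainly rule out a questionnaire. The registry could recover some outcomes.
- A reader might infer that patients are removed because they recover poorly. Poor neurological recovery is not a trigger, so the link between withdrawal and outcome is an assumption.
- A reader might infer that replacements are patients who fare better. They need only be eligible, and their course is unknown at enrolment.
- The normal model fits the ordinal ASIA grade poorly, because patients who remain at grade A share a floor. At 20 patients the standard error of a correlation of 0.50 is about (1 − 0.25)/√19 = 0.17, larger than the illustrated shifts of 0.03 to 0.10.
- The primary objective uses recordings from the intensive care stay and does not depend on 12-month outcomes.
- How recordings made before withdrawal enter the analysis can be left to an analysis plan.

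The gap itself remains. After an investigator termination the protocol names the data to be kept and then replaces the patient, and functional outcome is not among those data. Sampling error does not excuse an avoidable selection, least of all one that the replacement rule makes hard to see.

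**Conclusion.** The point holds in a limited form. For patients whose participation the investigator ends, the protocol provides for adverse-event capture and replacement but not for functional assessment to 12 months. Secondary objectives 2 and 3 are exposed; the primary objective is not.

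The direction and size of any bias depend on whether such terminations follow a poor course, which the protocol does not settle. Bias is nil if they are unrelated to outcome. Under the assumed models, a correlation of 0.50 would appear as 0.47 to 0.40, with the slope at 88% to 65% of its true value, or the share improved would be overstated by about 2 to 9 points. These ranges show what is possible and are not estimates for this trial.

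The change is worth making because it is cheap and the missing assessments cannot be recovered later.

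**What to change.** In Section 5.4, separate two situations:

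1. **Monitoring or study procedures ended by the investigator.** Keep the recordings already made and complete the scheduled ASIA, FIM and QLI-SCI assessments to 12 months unless the patient declines.
2. **Consent to follow-up withdrawn.** Use the data up to withdrawal and collect only what the patient still agrees to.

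Report the outcomes of replaced patients alongside the others, with the number replaced and the reasons. Align the POD#1 to POD#5 check in Section 6.2 so that it uses the same two categories.

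Leave the triggers for ending monitoring as they are. The sponsor should only reconcile the reference in 5.4 to newly developed criteria with those in 5.2 that are worded as pre-existing or as history.

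The cost is amendment wording in 5.4 and 6.2, and follow-up visits for a few patients that are already in the schedule for everyone.

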### **5.5 Premature Termination or Suspension of the Study**

This study may be suspended or prematurely terminated if there is sufficient reasonable cause. Written notification, documenting the reason for study suspension or termination will be provided to the REB.

Circumstances that may warrant termination include, but are not limited to:

- determination of unexpected, significant or unacceptable risk to patients
- insufficient adherence to protocol requirements
- data that are not sufficiently complete
- determination of futility

## 6. Study Schedule

### **6.1 Schedule of Evaluations**

See Appendix 1.

### **6.2 Description of Evaluations**

**Screening Visit and Informed Consent (Day 0 to Day 1)**

All patients admitted to the surgical intensive care unit at Health Sciences Center will be screened for potential enrollment in the study. The admission lists will be reviewed to identify patients with a spinal cord injury and patients that may be potential candidates for enrollment will be consented on a screening consent form. Thereafter, hospital records will be reviewed to verify whether the patient meets any inclusion or exclusion criteria. Initial screening may also require that the patient be examined to verify cognitive status and level of consciousness.

All patients deemed eligible for participation in the study will then be consented by a study coordinator through direct patient visit in the SICU. During this visit, study participates will also be given contact information for the study coordinator and a schedule for study visits.

Patients admitted on the weekends may not be eligible for the study as study personnel and necessary equipment may not be available

**Baseline Enrollment Visit (Day 0 to Day 1)**

After obtaining consent, study personnel will:

- perform an initial clinical assessment to obtain patient’s medical history
- conduct a physical examination
- verify medications and document laboratory investigations
- record vital signs for the patient
- review clinical exam and radiographic imaging studies to derive injury classification score using TLICs or SLICs scoring systems (all patients will need CT scan of spine and MRI of spine within first 24hours of arrival to SICU)
- administer ASIA impairment scale assessment (an objective scoring system to document level of spinal cord injury)
- administer patient questionnaires including Functional Independence Score and Quality of Life Index for Spinal Cord Injury (QLI-SCI)

**Surgical Treatment Visit (Day 0 to Day 3)**

- complete anesthesia log following termination of surgery
- complete intraoperative intraspinal pressure monitoring form
- complete intraoperative neurophysiological recordings form
- document any intraoperative adverse events using the intraoperative adverse event form

**Intraspinal Pressure Monitoring Visits (POD#1 to POD#5)**

Following surgery, each patient will be visited daily to conduct the following study related procedures:

- ensure no change to clinical status of the patient that would warrant termination of that patient’s involvement in the study
- verify that the intrapsinal pressure monitor is in situ and recordings are being captured continuously
- verify continuous monitoring of physiological data
- conduct transcranial magnetic motor evoked potential testing and record findings on neurophysiological monitoring report form
- document any medical or surgical adverse events
- document any protocol violations -document laboratory investigations including blood chemistry, hematology and medication use.

**Postoperative Inpatient Visits (POD#6 to 29)**

- on POD#6, the intraspinal pressure monitor will be removed at the bedside by study personnel
- medical or surgical adverse events will be recorded

**Follow Up Visits (POD#30, 3, 6, and 12 months following surgery)**

- functional assessment questionnaires will be administered including ASIA impairment scale, Functional Independence Score (FIM) and Quality of Life Index for Spinal Cord Injury (QLI-SCI).
- medical and surgical adverse events will be recorded in preceding time window will be noted
- functional progress with rehabilitation will be documented on the Physical Therapy and Rehabiliation form
- any readmissions (where study personnel were not otherwise notified) will be recorded.

**Study Close Out (12 month follow up visit)**

Patients will be followed for one year following surgery. At the end of this time period, patients will be given a letter to document termination of their involvement in the study. Study patients will be counseled to refer any further adverse events to either the Physical Medicine and Rehabilitation Physicians or to their Spine Surgeon.

At the termination of the study, a synopsis of the study results will be mailed to the study participants along with contact information for study personnel if they have any questions or concerns.

Further management issues and follow up will be done according to the standard practices of the involved surgeon, surgical team and nursing staff.

At the conclusion of the trial, all study forms, manuals and documentation (electronic and hard copies) will be stored in a secure location at the Foothills Medical Centre (exact location to be determined). Final data checks should be completed within six weeks of study termination after which the data set will be frozen for the purposes of final analysis. Mortality and morbidity checks will also be performed at this time and will be reported to the local Research Ethics Board. Study data, forms or manuals will not be made available to outside parties until the final manuscript has been completed and unless all primary investigators agree to disseminate this information. In the case where the study is terminated to the patient safety concerns, patients will be notified immediately about the reason for cessation of the trial by study personnel.

